### Current practice for goal setting and goal planning at Toronto Rehab

Goal setting and planning form an important part of care at Toronto Rehab. Goal setting is a patient-centred and collaborative process [27,28,35,36] wherein, upon admission to rehabilitation, the patient discusses goals with the interprofessional care team. Goals identified at this stage of care might be broad; e.g. “I want to be able to walk better”. Through discussion, the team explores the relationship of the individual’s goal and the impact of their condition within the context of participation and important life roles; e.g. “I want to be able to continue to provide childcare to my grandson, including walking him to school.” This part of the goal-setting and planning process is often termed ‘goal negotiation’ [27]. The individual therapists then work with the patient to identify specific and challenging [24,28] sub-goals at the activity or impairment level that would lead to progressive achievement of the larger goal; e.g. “I want to be able to walk 100m without stopping”. Each individual therapist then bases their therapeutic intervention on the patient’s identified goals. The goal coordinator, who is a member of the interprofessional team, meets with the patient once every two weeks to discuss progress towards all of his/her goals. Each individual therapist also meets with the patient routinely during daily therapy sessions to discuss progress relevant to his/her practice; i.e. physiotherapists would discuss progress towards walking goals with patients on a regular basis. During either the fortnightly meetings with the goal coordinator, or discussions with the patient’s therapists, sub-goals may be re-evaluated depending upon how the patient is progressing towards his/her goals; e.g. a more challenging goal may be set if previous sub-goals have been achieved. Specific goals are documented for each patient in the clinical chart. Throughout rehabilitation and at the time of discharge, the individual therapist or goal coordinator determines if the patient’s goals were achieved (see Figure 1).

### The ABLE system – description, on-going development and pilot implementation

The ABLE system consists of two lightweight commercially-available triaxial accelerometers (Figure 3; Model X16-1C or X6-2mini, Gulf Data Concepts, LLC., Waveland, Mississippi, USA). The accelerometers are ‘self-recording’, such that data are stored directly on an internal microSD card without the need for an external data logger [19,37]. The accelerometers are affixed just above the ankles of both limbs using a breathable foam wrap that is Velcro® hook receptive (Pro Wrap, Fabrifoam, Exton, Pennsylvania, USA). The accelerometers record acceleration in three axes for the entire monitoring period in blocks of eight hours at 40 Hz. Our previous work [19] confirms that these parameters are sufficient for the purpose of whole-day ambulatory monitoring. Participants are instructed to only remove the accelerometers before going to sleep at night (to prevent discomfort), when showering, and when required to do so for medical testing (e.g. magnetic resonance imaging).

**Figure 3 F3:**
[figure not shown]
**The ABLE accelerometers.** The ABLE accelerometer as affixed to the ankle above the lateral malleolus. Model X6-2mini is shown. In panel **A**, the accelerometer is exposed to show its size. In panel **B**, the accelerometer is covered by the foam wrap; this is how the accelerometers are affixed in practice.

Data are transferred from the accelerometers and processed using a custom-written algorithm [19] (MatLab, The Mathworks, Natick, Massachusetts, USA). The raw acceleration data are high-pass filtered at 0.25 Hz to remove the gravity component [38] and low-pass filtered at either 5 Hz for the purpose of step detection or 10 Hz to detect the temporal features of each step (i.e. heel strike and toe off) [19]. A bout of walking is defined by at least 4 consecutive steps with <10 s between steps; if there is a pause of 10 s or more between steps a new bout is identified. The following measures are calculated for each walking bout: number of steps taken, total bout duration, average cadence (steps per minute), and average swing duration (heel strike minus toe off) for each limb. Heel-strike and toe-off detection has previously been validated against foot-switches [19]. On-going development aims to determine the validity of calculating step length, walking speed and distance walked for each bout.

### Intervention

Participants will be recruited into the study when they are deemed to be ambulatory without supervision. Patients with stroke tend to be discharged from in-patient rehabilitation 2–4 weeks after they reach this status. Therefore, the length of the in-patient intervention phase will vary between participants but will be approximately 2–4 weeks long. Out-patient rehabilitation services are offered in three blocks of 4–6 weeks duration; the first block is 6-weeks long to allow extra time for assessment prior to prescription of rehabilitation services. Participants in this study will be followed only for the first and second (if applicable) block of out-patient rehabilitation. The third block is often either not completed at all or not completed immediately subsequent to the second block (i.e. there may be a gap of a number of months between the second and third block). Therefore, the duration of the out-patient phase of the intervention is 6–10 weeks.

In order to ensure that all physiotherapists administer the intervention in a consistent manner, we will host a series of in-services concerning goal-planning of walking activity. These in-services will focus specifically on the output from the ABLE system, which is the new component of this study. Physiotherapists will learn how to interpret the output from the ABLE system and how to use this information to evaluate a patient’s progress towards their goals. Specific cases will be discussed based on pilot testing of ambulatory monitoring.

#### In-patient rehabilitation phase

Participants in both intervention groups will meet with their primary treating physiotherapist once per week to discuss progress towards their goals for rehabilitation that are relevant to physiotherapy, including goals for walking. All participants will wear the accelerometers every weekday during in-patient rehabilitation to monitor daily walking activity. Research personnel will meet with the patients each morning to ensure that the accelerometers are worn correctly.

For those participants assigned to the feedback group, physiotherapists will receive a daily summary of patients’ walking activity as a tool to guide goal planning. Physiotherapists will use the information as a ‘homework checker’ to determine if patients are complying with an assigned walking program. In the case of non-compliance, the physiotherapist will discuss a coping strategy for better integrating walking activity into the patients’ day. In the event that the patient is meeting their specific sub-goals for walking activity, the physiotherapist will re-evaluate these sub-goals and suggest more challenging goals.

For participants assigned to the control group, physiotherapists will not receive accelerometer-based feedback of daily walking activity. However, physiotherapists will still discuss the achievement of walking goals with their patient. The same strategies implemented in the feedback group will be implemented in the control group (i.e. action plans, coping strategies, re-evaluation of goals). This process is no different to usual care around goal planning at Toronto Rehab.

#### Out-patient rehabilitation phase

Participants in both groups will meet with their primary treating physiotherapist regularly to discuss progress towards walking goals. All participants will wear the accelerometers daily during out-patient rehabilitation. For those in the feedback group, physiotherapists will receive a weekly summary of patients’ walking activity as a tool to guide goal planning. Participants in the control group will attend goal-planning meetings with their physiotherapists, as is usual care.

### Measures

A summary of the measures collected at each point in the study is included in Table 1.

**Table 1 T1:** Measures collected at the assessment time points

	**Time 1: study enrolment**	**Time 2: discharge from in-patient rehabilitation**	**Time 3: discharge from out-patient rehabilitation**	**Time 4: three months post-discharge from out-patient**
Demographic information	✓			
Stroke information	✓			
Medical conditions	✓	✓	✓	✓
Falls	✓	✓	✓	✓
Chedoke-McMaster Stroke Assessment	✓	✓	✓	
Berg balance scale	✓	✓	✓	
Activity-specific balance confidence questionnaire	✓	✓	✓	
National Institutes of Health Stroke Scale	✓			
Ambulatory monitoring	✓ (3 days)	✓ (3 days)	✓ (7 days)	
Spatio-temporal features of walking	✓	✓	✓	
Stroke self-efficacy questionnaire	✓	✓	✓	✓
Goal attainment		✓	✓	
Satisfaction with progress towards goals		✓	✓	
Community integration questionnaire			✓	✓
Barriers to walking interview	✓	✓	✓	✓

#### Cohort descriptors – demographics, medical & stroke history, and measures of physical function

The following demographic and medical information will be obtained from clinical charts on admission to rehabilitation in order to characterize the study cohort: age, sex, height, weight, date of stroke onset, lesion location, pre-morbid medical history & current medical conditions, prescription medications, the National Institutes of Health Stroke Scale (NIH-SS) [39], the Chedoke-McMaster Stroke Assessment (CMSA) [40] foot and leg scores, Berg Balance Scale (BBS) [41], and the Activity-specific Balance Confidence (ABC) questionnaire [42]. The NIH-SS is an 11-item scale that provides a gross measure of the effects and severity of stroke. The NIH-SS has shown good intra-rater (intraclass correlation coefficients; ICCs = 0.93) and inter-rater (ICCs = 0.95) reliability [43]. The CMSA assigns a score according to the level of motor recovery in the foot and leg and is frequently used to evaluate level of motor recovery post-stroke in clinical settings. The CMSA foot and leg scores have good intra-rater (ICCs = 0.94-0.98) and inter-rater (ICCs = 0.85-0.96) reliability [40]. The BBS is a 14-item observational rating scale that provides a measure of functional balance. Participants are asked to perform each of the 14 tasks and their ability to perform the task is rated on a scale from 0–4. The BBS shows good internal consistency (Cronbach’s α=0.92-0.98) and good inter-rater (ICCs = 0.95-0.98), intra-rater (ICCs = 0.97) and test-retest (ICC = 0.98) reliability post-stroke [44]. The ABC is a 16-item questionnaire that asks individuals to rate confidence performing various daily activities. The ABC shows good internal consistency (Cronbach’s α=0.94) and test-retest reliability (ICC = 0.85) in individuals post-stroke [45].

In addition to collection at admission to rehabilitation, medical conditions will be reviewed at all assessment time points to confirm that there have been no major changes in medical status between assessments. The CMSA, BBS, and ABC will be repeated at discharge from in-patient and out-patient rehabilitation as impaired balance control, impaired lower-limb function and reduced balance confidence could potentially be barriers to independent ambulation. The occurrence of falls will be documented for safety monitoring purposes.

#### Primary outcomes – daily walking activity & control of walking

The primary outcome measures pertain to walking activity as averaged over three days around the first two assessment time points (i.e. enrolment into the study and discharge from in-patient rehabilitation), and over seven days before the last assessment time point (discharge from out-patient rehabilitation). A longer monitoring period will be used for the out-patient phase as patients have more options for mobility post-discharge. Summary, whole day, outcome measures will be used in the analysis; i.e. total walking duration, total number of steps taken and total distance walked. However, it is most relevant to community ambulation and aerobic fitness to show increased duration of continuous walking [46,47]; therefore, we will also calculate the frequency and duration of longer walking bouts (i.e. >5 minutes continuously). Furthermore, intensity of walking is also important for cardiovascular benefit; therefore we will determine the frequency and duration of ‘high intensity’ walking, defined by either a walking speed or cadence ≥ 85% of maximum walking velocity.

Increased walking practice should improve control of walking. Spatio-temporal features of self-selected walking will be measured using a 4 m-long pressure sensitive mat (GAITRite, CIR Systems, Inc, Havertown, Pennsylvania, USA). Participants will start walking at least 1 m away from the mat and will be instructed to walk across the mat until they reach a mark 1 m from the end of the mat. Participants will be instructed to walk at their normal pace. Participants will complete three passes across the mat and measures will be averaged across the three passes. Walking speed, cadence, step length, and symmetry of spatio-temporal measures [48] will be calculated. While it is possible to determine these measures from the daily walking activity collected using the ABLE system, standardized assessment is required for pre- to post-intervention comparison of spatio-temporal measures.

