### Statistical analyses and sample size

The following potentially confounding measures will be compared between the two intervention groups: CMSA, BBS, NIH-SS, ABC, and length of stay (in-patient rehabilitation). Measures that differ significantly between the two groups will be included as covariates in statistical models comparing interventions. Repeated-measures analysis of variance (ANOVA) or analysis of covariance (ANCOVA; as appropriate), with group-by-time interaction, will be used to evaluate the effect of the interventions on walking activity, spatio-temporal characteristics of walking, and SEQ. Separate ANOVAs will be used for each outcome measure. The ‘group’ term is the intervention group; the ‘time’ term is the assessment time point. The group-by-time interaction effect will reveal if there is a greater change over time in one group compared with the other. Separate analyses will be conducted to compare measures at the first three time points; i.e. discharge from in-patient will be compared to study enrolment, and discharge from out-patient will be compared to discharge from in-patient. One-way ANOVA or ANCOVA will be used to compare the CIQ and satisfaction between the two groups at discharge from rehabilitation and three months post-discharge from in-patient. The frequency of goal attainment between the two groups will be compared at discharge from both in-patient and out-patient rehabilitation; intent-to-treat analysis will be employed for this outcome for all participants initially randomized, including those who withdraw from the study [24,57]. Barriers to walking will be documented.

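### The Time 3 versus Time 2 walking comparison sets a seven-day mean that includes a weekend against a three-weekday mean, so a feedback effect that differs by day type would read as a change of effect over time

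*Protocol article*

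**What the plan says.** Four places in the protocol article's Methods bear on this.

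- **In-patient recording** (In-patient rehabilitation phase): "All participants will wear the accelerometers every weekday during in-patient rehabilitation to monitor daily walking activity".
- **Out-patient recording** (Out-patient rehabilitation phase): "All participants will wear the accelerometers daily during out-patient rehabilitation".
- **Averaging windows** (Primary outcomes): walking activity is "averaged over three days around the first two assessment time points", that is, enrolment (Time 1) and in-patient discharge (Time 2). For out-patient discharge (Time 3) it is averaged "over seven days before the last assessment time point (discharge from out-patient rehabilitation"). Table 1 gives the same 3, 3 and 7 days. The reason offered is: "A longer monitoring period will be used for the out-patient phase as patients have more options for mobility post-discharge".
- **Analysis** (Statistical analyses and sample size): the planned pairs are "discharge from in-patient will be compared to study enrolment, and discharge from out-patient will be compared to discharge from in-patient". The stated reading of the test is: "The group-by-time interaction effect will reveal if there is a greater change over time in one group compared with the other".

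**The concern.** The Time 2 window can hold no weekend day, because none is recorded in hospital. A run of seven days at Time 3 always holds two. The stated reason for lengthening the window concerns mobility after discharge and does not touch the change in the mix of days.

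The second-phase test asks whether the groups diverge or converge between the two discharges. Feedback reaches the patient through the physiotherapist, who uses the report to check an assigned walking programme and reset sub-goals. An effect that arises this way could be smaller on days without therapy contact, or larger on days with more room for practice at home. If it differs by day type, an effect that is fully maintained on comparable days could look weaker or stronger at Time 3, and the planned interpretation would call that a change over time. Only the accelerometer outcomes are exposed; gait on the pressure mat and the questionnaires do not depend on these windows.

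**Working it through.** **Inputs from the protocol article**

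- Weekend share of the window: 0/3 at Times 1 and 2; 2/7 (29%) at Time 3. This takes daily wear to mean every calendar day and the seven days to be consecutive.
- Target difference 20 minutes, SD of change 23 minutes, Type I error 0.05, Type II error 0.1, 28 per group.

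**The plan's own figure.** For the Time 1 to Time 2 change, two-sided:

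n = 2 × [23 × (1.960 + 1.282) / 20]² = 27.8, rounded up to 28 per group.

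The stated sample size is reproduced. It rests on matched three-day windows, so the day mix does not alter it.

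**What enters the interaction.** Let D be the feedback effect on weekdays and E the effect at weekends, both constant over time.

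- Group difference at Time 2: D.
- Group difference at Time 3: (5D + 2E)/7.
- Time 3 minus Time 2: (2/7) × (E − D).

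A weekend shift s common to both arms adds (2/7)s to each arm's Time 3 mean. It moves the time main effect and contributes 0 to the interaction.

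**Numbers.** D = 20 minutes, the protocol's target; E is assumed.

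| Weekend effect E | Effect in seven-day mean | Apparent change from Time 2 to Time 3 |
|---|---|---|
| 0 | 14.3 | −5.7 |
| 10 | 17.1 | −2.9 |
| 20 | 20.0 | 0 |
| 30 | 22.9 | +2.9 |

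**Against the noise.** If the SD of 23 minutes carries over to the Time 2 to Time 3 change (an assumption), SE = 23 × √(2/28) = 6.1 minutes. A shift of 5.7 minutes would reject the hypothesis of no change about 15% of the time, and 2.9 minutes about 8%, against a nominal 5%. Time 3 is taken only in those admitted to out-patient rehabilitation at the institution. The real SE is therefore likely to be larger and these rejection rates lower, but the shift itself is unchanged.

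**Time 3 against enrolment.** Before feedback starts, the expected difference between randomised groups is zero on any kind of day. The contrast would therefore estimate (5D + 2E)/7, which is the true whole-week effect. With E = 0, the 14.3 minutes is a correct answer to that question.

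**The case against.** The strongest reply is that both randomised arms change window in the same way, so the interaction removes any general difference between weekdays and weekends. That stands, and it limits the point to an effect that varies by day type. The documents give no evidence on whether it varies or by how much. Even the case of no weekend effect gives a shift of slightly less than one standard error.

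It is also fair to say that a full week is a sensible target for community walking, and that weekdays at home are not the same as weekdays in hospital: the setting changes, and reports go from daily to weekly. Matching weekdays removes only the day-mix part of the contrast. This is a good reason to keep the seven-day mean. It is not a reason to leave out the matched comparison, because the article fixes both windows and the contrast between them.

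A reader might infer three stronger points, which the documents do not support.

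- **That the primary comparison is biased.** Time 1 to Time 2 uses the same three-day window at both visits.
- **That any comparison involving Time 3, including one with enrolment, is distorted.** No such enrolment comparison is listed, and it would carry no day-mix artefact.
- **That recorded in-patient weekdays are wasted and Time 2 should use five.** The feedback arm's daily records serve the intervention. Extending Time 2 alone would unmatch it from Time 1 and move its centre back one weekday. If the 20-minute difference builds linearly over 10 to 20 in-patient weekdays, that costs 2 to 1 minutes. If day-to-day noise is 10–50% of the change variance, half of it from Time 2, the SD falls only from 23 to 23 × √0.98 = 22.8 or 23 × √0.90 = 21.8. The standardised effect goes from 20/23 = 0.87 to between 18/22.8 = 0.79 and 19/21.8 = 0.87, which is no gain. The linear build-up and the noise share are assumptions.

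**Conclusion.** The point holds for one contrast: "discharge from out-patient will be compared to discharge from in-patient", on the accelerometer outcomes. As planned, its interaction cannot separate a change of effect over time from a feedback effect that differs between weekdays and weekends. The size is (2/7) of the difference between weekend and weekday effects. That is −5.7 to +2.9 minutes over assumed weekend effects of 0 to 30 minutes with a 20-minute weekday effect, and zero if the effect is the same on all days. The extreme is 29% of the target difference and a little under one standard error at 28 per group. This is a limit on interpretation that costs little to remove, and it does not threaten the sample size or the first-phase result.

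**What to change.** For the Time 3 versus Time 2 comparison only, prespecify a like-for-like analysis in which the Time 3 value is the mean of the five weekdays inside the seven-day window. Report it beside the seven-day mean, which stays as the measure of whole-week community walking. State in advance that, if the two disagree, the seven-day interaction will not be read as a loss or gain of effect over time. Keep the matched three-day windows at Times 1 and 2.

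The cost is one extra analysis per accelerometer outcome, from days already recorded. The five-day value is somewhat noisier: the day-to-day part of its variance is 7/5 = 1.4 times that of the seven-day mean if days vary independently. Fixing the rule before outcome data are seen also prevents a later choice between the two results.

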#### Secondary outcomes – self- efficacy, community integration, goal attainment, satisfaction & barriers

The Stroke Self-Efficacy Questionnaire (SEQ) [49] will be used to measure stroke-specific self-efficacy. This 13-item questionnaire asks participants to rate confidence in completing various tasks, including walking indoors and outdoors and exercising, on a scale from 0–10. This questionnaire shows good test-retest reliability (ICCs > 0.87) [50], internal consistency, and criterion validity and can discriminate between patients who are independently ambulating and those who are not [49].

The Community Integration Questionnaire (CIQ) will be used as a measure of integration and participation post-discharge from in- and out-patient rehabilitation [51,52] and has been used often in stroke research [53-56]. This is a 15-item questionnaire that evaluates integration into the community in three domains: home, social, and productive activities (e.g. employment or volunteer activities). Researchers have developed a version of the CIQ specifically for individuals with aphasia and this version of the questionnaire shows excellent test-retest reliability in the post-stroke population (ICC = 0.96) [55].

Goal attainment will be determined from patient charts at discharge from both in-patient and out-patient rehabilitation. Goals are classified ‘achieved’, ‘partially achieved’, ‘not completed’, or ‘discontinued’. Satisfaction with progress towards goals will also be extracted from patient charts (rated on a 10-point scale). We will interview patients in order to determine barriers to walking. A single open-ended question will be used: “what, if anything, do you think is preventing you from walking more than you are at the moment?”.

